# Dry suction versus wet suction technique of endoscopic ultrasound-guided fine-needle biopsy for diagnosis of solid pancreatic lesions: study protocol of a multicenter randomized controlled non-inferiority trial

**DOI:** 10.1186/s13063-023-07842-8

**Published:** 2023-12-13

**Keywords:** EUS-FNB, Franseen needle, Wet suction, Dry suction, Solid pancreatic lesions, Diagnostic yield

## Abstract

**Background:**

Studies have shown that the wet suction technique in endoscopic ultrasound-guided fine-needle aspiration (EUS-FNA) generates better histological diagnostic accuracy and specimen quality than the dry suction technique. However, conclusions of wet suction on the diagnostic accuracy of endoscopic ultrasound-guided fine-needle biopsy (EUS-FNB) are still controversial. Besides, the optimal number of passes for EUS-FNB has not been determined. We aimed to design a large multicenter randomized trial to compare the diagnostic accuracy of dry suction versus wet suction technique in solid pancreatic lesions (SPLs) using 22G Franseen needles and determine the optimal number of passes required for EUS-FNB.

**Methods:**

This is a multi-center open-label, randomized controlled non-inferiority trial with two parallel groups. Two hundred patients with SPLs will undergo EUS-FNB using 22G Franseen needles in 4 tertiary hospitals in China and will be randomly assigned to the dry suction group and wet suction group in a ratio of 1:1. The primary endpoint is diagnostic accuracy. Secondary endpoints include the optimal number of needle passes, sensitivity, specificity, specimen quality, cytological diagnoses, time of the procedure, and incidence of complications.

**Discussion:**

This study has been designed to determine (i) whether EUS-FNB using 22G Franseen needle with dry suction is non-inferior to wet suction in terms of diagnostic accuracy and (ii) the optimal number of passes during EUS-FNB of SPLs using 22G Franseen needle.

**Trial registration:**

ClinicalTrials.gov NCT05549856. Registered on September 22, 2022.

**Supplementary Information:**

The online version contains supplementary material available at 10.1186/s13063-023-07842-8.

## Background

Endoscopic ultrasound-guided fine-needle aspiration/biopsy (EUS-FNA/B) is an efficient diagnostic technique for solid pancreatic lesions (SPLs). Compared with FNA needles, the FNB needles can obtain much more core tissue, making histological investigations and genetic testing widely used, contributing to precision medication.

A novel wet suction technique for EUS-FNA was developed to improve the quality of aspirates and reduce blood contamination for diagnosis performance [1]. For the “wet suction” technique, the needle was flushed with saline solution to replace the column of air and then aspiration with a-10 ml pre-vacuum syringe. This is based on the principle that water is a less compressible fluid compared to air. Therefore, the volume of the vacuum could be enhanced when the EUS needle is filled with water (wet technique) [2]. A recent, randomized trial by Yun W. et al. has demonstrated that EUS-FNA using the wet technique is superior to the standard method in terms of diagnostic accuracy, sample adequacy, and sample blood contamination [3]. However, there are few studies on the impact of wet aspiration on the diagnostic accuracy of EUS-FNB. The sample size of these studies is small, and the conclusions are controversial.

The 2017 European Society for Gastrointestinal Endoscopy (ESGE) guidelines suggest the performance of two to three passes with an FNB needle when on-site cytologic evaluation is unavailable [4]. An RCT study demonstrated that the diagnostic accuracy of EUS-FNB alone with 3 needle passes in patients with SPLs reached 97.4% [5]. Of note, a recent large-scale multicenter RCT study showed that the overall diagnostic accuracy of FNB for SPLs was 94.7%, with an average of 2.81 passes required [6]. Unlike the reverse bevel needle, a needle with Franseen geometry was used in this study, and a meta-analysis showed that the Franseen needle was significantly superior to the reverse-bevel needles in both diagnostic accuracy and sample adequacy [7]. Further research is needed to explore the optimal needle passes of EUS-FNB using the Franseen needle.

The purpose of this multicenter RCT study is to compare the diagnostic accuracy of the dry suction technique versus the wet suction technique in SPLs using a 22G Franseen needle and determine the optimal passes required for EUS-FNB. This study may provide high-level evidence of EUS-FNB procedures for clinical practice.

## Methods

### Study design

This is a multicenter, open-label, randomized controlled non-inferiority trial with two parallel groups. Two hundred patients with SPLs will undergo EUS-FNB using 22G Franseen needles in 4 tertiary Chinese hospitals and will be randomly assigned to the dry suction group and the wet suction group in a ratio of 1:1. A checklist with the recommendations for Interventional Trials (SPIRIT) is attached as Additional file 1. Study flowchart and standard protocol items displaying the trial’s enrollment, intervention, and assessment schedules were showed in Figs. 1 and 2, respectively.

**Fig. 1 Fig1:**
[figure not shown]
CONSORT flowchart. Asterisk (*) symbol indicates the following: we will follow-up with all patients for postoperative complications after the procedure within 24 h and 72 h. If the pathologic diagnosis of EUS-FNB samples is obtained during the punctures, we will observe at follow-up 1 year later

**Fig. 2 Fig2:**
[figure not shown]
Standard protocol items Recommendations for Interventional Trials (SPIRIT): schedule for data collection. Superscript digit one (^1^) indicates the following: blood tests to be performed include blood routine test, total bilirubin, direct bilirubin, indirect bilirubin, INR, and CA-199. Superscript digit two (^2^) indicates the following: clinical signs include pain, weight loss, jaundice, etc. Superscript digit three (^3^) indicates the following: adverse events include unfavorable events and adverse reactions not related to the EUS-FNB procedure

### Ethics approval and patient consent

The study was approved by the ethics committee of NanFang Hospital of Southern Medical University (NFEC-2022–335) on 1 September 2022. Subsequently, the ethics committee of each participating hospital approved the trial. At each participating center, the study investigators will obtain informed consent from the candidates. The trial was registered at Clinical Trials.gov with identifier No. NCT05549856.

Participants will provide informed consent to the sampling of biological material(pancreatic lesions), which will be deidentified and stored in the secure research facilities of the participating trial sites. Consent for the necessary processing of the samples such as medical photography and preservation, pathology examination, and medical waste disposal is addressed.

### Outcomes

The primary outcome is to compare the rate of diagnostic accuracy of EUS-FNB using the two different suction techniques (dry suction and wet suction). The rate will be calculated as the sum of true positive values and true negative values divided by the total number of samples, with an accurate diagnosis defined as a final diagnosis consistent with the tissue sample obtained during the needle passes.

The secondary outcomes include the optimal number of needle passes, sensitivity, specificity, specimen quality, cytological diagnoses, time of the procedure, and incidence of complications. Specificity analysis is only applicable to participants without malignancy, whereas sensitivity analysis is only applicable to persons with malignancy.

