### Randomization and blinding

Patients will be evaluated by gastroenterologists, surgeons, oncologists, and endoscopists. The potential candidates will be informed and enrolled in this trial by our study team. Stratified blocked randomization was used in the present study. The list of random numbers was generated by an independent statistician who was blinded to this study using the R software (v 4.0.3) by block with stratification on gender. The patients will be allocated randomly to either the dry suction group or the wet suction group in a ratio of 1:1 according to random numbers. To prevent different subject recruitment rates at the various hospitals from interfering in the development of the study, each center will use its list, and the entire population will be randomized in blocks between the two groups.

We used sequentially numbered sealed opaque envelopes to conceal allocation. The cytologists and the pathologists will be blinded during the entire study.

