### Specimen

After 3 needle passes, the doctor will evaluate the adequacy of the sample with macroscopic on-site evaluation (MOSE) and decide whether to continue additional punctures. MOSE was performed by gross visualization of the collected material by the endoscopists and considered adequate when a white/yellowish aggregate core longer than 10 mm was retrieved. Three needle passes at least were required for both groups. The specimens obtained at each pass will be marked and sent to pathology separately. It is to be evaluated using traditional cytological smear, liquid-based thin layer cytological examination, and histological examination for each pass.

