### Sample size calculation

The sample size calculation was based on the primary outcome of diagnostic accuracy for the evaluation of solid pancreatic lesions. The reported diagnostic accuracy of EUS-FNB for SPL using dry suction is approximately 96.2%, and the wet suction technique is about 98.3% in the literature [6, 8]. Based on the reported data and the clinical judgment, the non-inferiority of dry suction in EUS-FNB will be assessed with a non-inferiority (*δ*) margin of 10%. With a two-sided test, a significance level of 2.5% (*α* = 0.025), and a power (1 − *β*) of 90%, using the PASS 15.0 software and a sample allocation ratio of 1:1 between the dry suction and wet suction groups, 180 patients should be enrolled. Considering a 10% dropout rate, a final sample of 200 participants (100 per group) is needed.

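### The primary accuracy rate is defined per sample, although the trial randomises, diagnoses and sizes by patient and each patient gives at least three separately examined samples

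*Protocol article*

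**What the plan says.** All references are to the protocol article.

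- **Outcomes**, on the primary rate: "The rate will be calculated as the sum of true positive values and true negative values divided by the total number of samples". The sentence goes on to describe "an accurate diagnosis defined as a final diagnosis consistent with the tissue sample obtained during the needle passes". The same section applies sensitivity to people with malignancy and specificity to participants without it.
- **Specimen**: "Three needle passes at least were required for both groups". After the third pass the doctor judges adequacy by eye and may "decide whether to continue additional punctures". On handling: "The specimens obtained at each pass will be marked and sent to pathology separately". The examinations are a smear, "liquid-based thin layer cytological examination, and histological examination for each pass".
- **Randomization and blinding**: "The patients will be allocated randomly to either the dry suction group or the wet suction group in a ratio of 1:1".
- **Final diagnosis**: the reference standard, including what counts as a true or false negative, is set by type of patient.
- **Sample size calculation**: "180 patients should be enrolled", raised to 200 participants for 10% dropout.
- **Statistical analysis plan**: the two techniques are compared by a chi-squared test. The unit of analysis is not named.

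**The concern.** A primary endpoint needs one unit of analysis, and it should be the unit that was randomised and powered. Here the formula names samples while the rest of the design works with patients. The separate examination of each pass makes the literal reading workable. The per-pass data will exist in any case, because the optimal number of passes is a secondary outcome, so both a per-pass and a per-patient accuracy could be computed and reported under the same name.

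If the literal reading were followed, three things would change:

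- The estimate would be accuracy per pass, which is a different quantity from accuracy per patient.
- A patient with five passes would count 5/3 as much as one with three. Extra passes are decided after randomisation, in an open-label trial, by the endoscopist, who applies a stated visual criterion but knows the technique.
- An ordinary chi-squared test would treat several results from one lesion, judged against one final diagnosis, as independent. Positive correlation would make the standard error too small. In a non-inferiority trial that raises the risk of a false claim of non-inferiority.

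**Working it through.** **1. Which unit each part of the plan uses**

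| Part of the plan | Unit |
|---|---|
| Primary rate, denominator (Outcomes) | sample |
| Primary rate, meaning of accurate (Outcomes) | unclear; can be read as the combined yield of all passes |
| Sensitivity and specificity (Outcomes) | patient |
| Allocation (Randomization and blinding) | patient |
| Final diagnosis (Final diagnosis) | patient |
| 180 and 200 (Sample size calculation) | patient |
| Chi-squared test (Statistical analysis plan) | not stated |

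**2. Reproducing the sample size.** Inputs from Sample size calculation: wet 98.3%, dry 96.2%, margin 10 points, alpha 0.025, power 90%, ratio 1:1, dropout 10%. With one independent result per patient, one-sided alpha and unpooled variance:

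n per arm = (1.960 + 1.282)² × (0.983 × 0.017 + 0.962 × 0.038) / (0.10 − 0.021)²

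= 10.51 × 0.05327 / 0.006241 = 89.7, so 90 per arm and 180 in all. Then 180 / 0.9 = 200.

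The stated figures are reproduced exactly with one result per patient. (The article calls the 2.5% test two-sided, but 180 is reached with a one-sided 2.5%. That is a separate point.)

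**3. What the literal denominator would be.** At the minimum of three passes, 90 evaluable patients per arm give 90 × 3 = 270 samples, or 540 in all. The full 100 per arm give at least 300 per arm.

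**4. Effect of ignoring the correlation.** The article gives no intra-patient correlation (ICC), so a range of 0.2 to 0.5 is assumed, with exactly three samples per patient.

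- Design effect: DE = 1 + (3 − 1) × ICC
- Effective number per arm: 270 / DE
- True one-sided error of a nominal 2.5% test: 1 − Φ(1.96 / √DE)

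| Assumed ICC | DE | Effective n per arm | True one-sided error |
|---|---|---|---|
| 0.2 | 1.4 | 193 | 4.9% |
| 0.3 | 1.6 | 169 | 6.1% |
| 0.5 | 2.0 | 135 | 8.3% |

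The same factor applies to a confidence interval for the difference: its width would be understated by 1/√DE, that is 0.85 at ICC 0.2 and 0.71 at ICC 0.5. With no correlation the error stays at 2.5%. Any positive correlation raises it.

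**The case against.** The strongest reply is that samples is loose wording and that a per-patient rate was meant throughout. There is good support for this:

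- The second half of the defining sentence speaks of a single tissue sample from several passes.
- The Specimen section uses the singular for the material judged after three passes, and calls the separately labelled items specimens. Usage is not uniform, however: the Fig. 1 legend and the data management section also say samples.
- True and false negatives are assigned by patient. A per-pass accuracy beside per-patient sensitivity and specificity would not come from the same two-by-two table.
- The sample size works out exactly with one result per patient.

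All of this stands as evidence of intention. It does not remove the conflict, because the formula names its denominator outright and nothing in the article overrides it. A full analysis plan may well hold the rule for combining passes, and its absence from an article is not the finding. The finding is that the formula as printed disagrees with the design.

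A reader might infer that the trial plans a chi-squared test on pooled samples, and so has an inflated error rate. The documents do not support that. The analysis section names the test but no per-sample data set, and the inflation appears only when the literal formula is joined to that test under an assumed correlation. Nor does the article say whether the cited 96.2% and 98.3% are per-patient rates. Any loss of power for a per-pass endpoint would need a further model and a scoring rule that the article does not give, so none is claimed here.

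**Conclusion.** The point holds as an error in the stated primary-endpoint formula. If a per-patient rate is intended, the denominator is misstated. If a per-sample rate is intended, it is not the endpoint that was powered, and a test assuming independence does not fit it. The text needs correcting in either case.

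The size of the consequence is conditional. The true one-sided error of 4.9% to 8.3%, against a nominal 2.5%, requires the literal reading, a test that ignores clustering, three samples per patient, and an ICC of 0.2 to 0.5, which is an assumption. Under the per-patient reading there is no inflation, and the 180 and 200 stand. The correction should be made before analysis. It does not call the design or the sample size into question.

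**What to change.** In the primary outcome definition, replace the denominator of samples with the total number of patients analysed. State that each patient contributes one EUS-FNB result, formed from all passes by a pre-stated rule that covers passes which disagree. Leave the analysis population as the Statistical analysis plan section defines it.

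Use per-pass results only for the secondary outcome on the number of passes, with an analysis that allows for correlation within patients.

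The cost is a sentence or two. The sample size, the conduct of the trial and the data collected do not change. Because the trial is open-label and per-pass data will be available, the rule should be fixed before accuracy is examined by arm.

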### Eligibility criteria

#### Inclusion criteria

The inclusion criteria for trial eligibility are as follows:Age from 18 to 85 yearsDiagnosis or suspicion of a solid pancreatic lesion based on previous imaging examination (ultrasonography, computed tomography [CT], or magnetic resonance imaging [MRI])Written informed consent obtained

#### Exclusion criteria

The exclusion criteria are the following:Any condition that could prevent endoscope insertion or EUS-FNB procedureThat no pancreatic lesion on EUSUse of anticoagulants/antiplatelet drugs that cannot be discontinuedCoagulation disorder: international normalized ratio (INR) > 1.5 or platelet counts < 50,000/mm^3^Pregnancy or patients with mental disordersOther medical conditions make the patient unsuitable for ineligibilityInability or refusal to provide informed consent

### Randomization and blinding

Patients will be evaluated by gastroenterologists, surgeons, oncologists, and endoscopists. The potential candidates will be informed and enrolled in this trial by our study team. Stratified blocked randomization was used in the present study. The list of random numbers was generated by an independent statistician who was blinded to this study using the R software (v 4.0.3) by block with stratification on gender. The patients will be allocated randomly to either the dry suction group or the wet suction group in a ratio of 1:1 according to random numbers. To prevent different subject recruitment rates at the various hospitals from interfering in the development of the study, each center will use its list, and the entire population will be randomized in blocks between the two groups.

We used sequentially numbered sealed opaque envelopes to conceal allocation. The cytologists and the pathologists will be blinded during the entire study.

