### Participating sites

All four sites are large tertiary hospitals in China. To avoid biases derived from the learning curve, only the sites with annual EUS-FNA/FNB cases ≧ 100 have been invited to participate in the present study. Endoscopists experienced in interventional EUS, such as EUS-FNA/FNB more than 100 cases, performed the procedures. The Nanfang Hospital of the Southern Medical University is key in minimizing heterogeneity and centralizing decision-making in conflicts. During the conduct of the trial, the principal investigators will monitor the enrollment targets monthly, and the coordination meeting was organized periodically.

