### Statistical analysis plan

The full analysis set should be as close as possible to the intention-to-treat set. The direct deletion method will be used to treat missing data.

Continuous variables will be summarized as means with standard deviation and compared with *t*-tests or Wilcoxon rank-sum tests. Categorical variables will be expressed as percentages using the *χ*^2^ test or the Fisher exact test. Differences in diagnostic yield between the two techniques will be evaluated with the chi-squared test. Statistical significance will be considered for *P* < 0.05. All statistical analyses will be performed using SPSS (version 25.0, IBM, Armonk, NY).

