## Discussion

There are several variables affecting the outcomes of EUS-FNA/FNB, including needle selection, operator experience, adequacy of sample, use of suction, the number of needle passes, and the presence of ROSE. Increasingly studies have reported that the Franseen needle can provide higher diagnostic yield and accuracy compared to other needle types, particularly for SPL [7, 9, 10]. The wet suction technique in EUS-FNA has been proven to reduce blood contamination and increase diagnostic yield [2, 3]. An RCT study found that EUS-FNB with wet suction resulted in a significantly better quality of specimen, histological, and first-pass diagnostic yields compared with the dry suction, but they used 5 ml negative pressure, which differed from the standard negative pressure previously reported [11]. Another study has shown that EUS-FNB using the slow pull, wet technique, or standard technique makes no significant difference in terms of specimen quality or the number of needles required to obtain a diagnosis. However, the study was a single-center study which was early terminated, resulting in inadequate sample size and convincing data [12].

In the previous RCT, dry suction versus wet suction was only compared during EUS-FNA procedure. There was no data for EUS-FNB using Franseen needle. In our study, we will compare the diagnostic accuracy of dry suction versus wet suction technique, and we also explore the optimal numbers of passes for SPLs. Smaller numbers of needle passes will be beneficial to patients in terms of procedure time, unnecessary passes, and risk of complications. We chose a non-inferiority design based on the expectation that dry suction of EUS-FNB is as good as wet suction and the dry suction can simplify the procedure and shorten the procedure time. With the improved performance of needles, satisfactory diagnostic accuracy of EUS-FNB in SLPs may be achieved only by dry suction and limited needle passes.

This study design has some limitations. First, this study will be performed in a multicenter setting; the bias between operators may still exist despite the training on standardized processes for all centers. Large sample size and randomization have been used to counteract this possible bias and to obtain results that allow for extrapolation to the general population.

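### Allocation is blocked by sex within centre lists, but the stated chi-squared comparison ignores the strata and gives no interval to hold against the 10-point margin; the effect on precision is small

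*Protocol article*

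**What the plan says.** Under Randomization and blinding, the article describes stratified blocked randomisation, with the list generated "by block with stratification on gender". The same section says that "each center will use its list, and the entire population will be randomized in blocks between the two groups". Participating sites confirms the number of centres: "All four sites are large tertiary hospitals in China". Read together, these give centre-specific lists blocked by sex, hence up to 4 x 2 = 8 strata.

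The Statistical analysis plan section says: "Differences in diagnostic yield between the two techniques will be evaluated with the chi-squared test". It names no stratum, covariate or stratified estimator, and it describes no confidence interval for the difference between arms. The Sample size calculation section sets a non-inferiority margin of 10%.

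The Discussion accepts that "the bias between operators may still exist despite the training on standardized processes for all centers" and answers: "Large sample size and randomization have been used to counteract this possible bias".

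**The concern.** An analysis should normally respect the restrictions imposed on the randomisation. If accuracy differs between strata, blocking within them removes part of the chance variation in the treatment difference. A single pooled table still counts that part, so its standard error is somewhat too large.

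The practical gap is in the form of the result. A non-inferiority claim needs a lower confidence limit for dry minus wet to compare with -10 points, and a chi-squared P value supplies none. If the analysis is to be respecified as an interval, it should be settled at the same time whether that interval follows the randomisation. What is at stake is consistency between design and analysis and a small amount of precision, not validity.

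**Working it through.** **Inputs.** From Sample size calculation: accuracy "using dry suction is approximately 96.2"%; wet suction 98.3%; margin 10 points; power 90%; alpha 0.025; 180 before dropout and 200 after. The documents give no centre accuracies or centre sizes, so those below are assumptions.

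**1. The plan's own figure.** n per arm = (z_alpha + z_beta)^2 x [p1(1-p1) + p2(1-p2)] / (margin - difference)^2
= (1.960 + 1.282)^2 x (0.983 x 0.017 + 0.962 x 0.038) / (0.100 - 0.021)^2
= 10.51 x 0.05327 / 0.006241 = 89.7, so 90 per arm and 180 in all; 180 / 0.9 = 200.
The figure reproduces as an unstratified calculation at one-sided 0.025, which corresponds to the lower limit of a 95% interval. (Read literally as two-sided 2.5%, it would be 212.)

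**2. Expected events.** 90 x 0.017 + 90 x 0.038 = 4.95 inaccurate diagnoses, which is about 1.2 per centre (4.95 / 4) or 0.6 per centre-by-sex stratum (4.95 / 8).

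**3. Variance gain from stratifying by centre.** For equal-sized centres, the relative reduction is var(centre accuracy) / [p(1-p)]. The planned standard error is sqrt(0.05327 / 90) = 0.0243, so the 95% half-width is 1.96 x 2.43 = 4.8 points. A reduction r shortens it by 4.8 x [1 - sqrt(1 - r)].

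| Assumed centre accuracies | Variance / p(1-p) | Reduction | Half-width shortened by |
|---|---|---|---|
| 96, 97, 97.5, 98% | 0.0000547 / 0.02792 | 0.2% | about 0.005 points |
| 92, 96, 98, 99% | 0.000719 / 0.03609 | 2.0% | about 0.05 points |
| 88, 95, 98, 99% | 0.00185 / 0.0475 | 3.9% | about 0.09 points |

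The first row has a mean of 97.1%, close to the planned pooled 97.25%. The other two have means of 96.25% and 95%.

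**4. Simulation with eight strata.** 100,000 trials per scenario, 90 per arm, assumed unequal strata, arms balanced within strata. Power is for the lower Wald limit above -10 points at the planned rates. Type I error is for the test of equality at a common accuracy of 97%.

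| Centre effect (control accuracy range) | Power, unstratified | Power, stratified | Type I, chi-squared | Type I, Cochran-Mantel-Haenszel |
|---|---|---|---|---|
| None (98.3%) | 85.9% | 86.4% | 4.5% | 4.6% |
| Moderate (95.6 to 99.2%) | 86.1% | 87.8% | 4.4% | 4.7% |
| Extreme (92.0 to 99.8%) | 86.6% | 90.5% | 3.9% | 4.7% |

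The estimated difference was identical with and without stratification. Part of the power gain is artificial, because the plug-in stratified standard error is too small in sparse strata. With no centre effect it averaged 0.0226 against an actual standard deviation of 0.0245. At a true deficit of 10 points (nominal 2.5%), the unstratified Wald limit wrongly passed 4.52% of trials with no centre effect and 3.35% in the extreme case; the stratified plug-in limit passed 4.80% and 5.08%.

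**5. Simulation stratified by centre only.** Four unequal centres, 90 per arm. With the Sato variance, power was 85.9% stratified against 85.9% unstratified with no centre effect, and 83.8% against 83.8% with a large one. A stratified Miettinen-Nurminen interval lost about 1 to 4 points of power against its unstratified form.

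**The case against.** The strongest objection is that this is a condensed article without the full SAP, and adjustment for stratification factors is commonly settled there. The quoted sentence also speaks of diagnostic yield, whereas the primary outcome is diagnostic accuracy. This has some force and keeps the point minor. But the article does name a test, and its general rule for categorical variables is also chi-squared or Fisher. Neither route is stratified, and neither gives an interval.

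It is also fair to say that the error runs in the safe direction and is tiny against a 10-point margin. That stands in full. So does the warning that eight strata with about 0.6 failures each are too sparse, which is why sex is left out of the fix.

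Three stronger readings may tempt a reader; the documents do not support them.

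- *The pooled comparison is biased by centre.* Blocked 1:1 lists within each centre already balance the arms there, and in the eight-stratum simulation the estimate did not change. Incomplete blocks, the 10% dropout allowance and deletion of missing data could disturb the balance of the analysed set. Nothing in the documents shows that this would be material.
- *Stratifying would deal with operator differences.* Operator is not a randomisation stratum. A centre-stratified analysis does nothing about differences between operators within a centre.
- *The protocol relies on randomisation alone.* The Discussion also cites training and sample size, and Participating sites requires experienced endoscopists.

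**Conclusion.** The mismatch is in the text: allocation is blocked by sex within centre lists, while the only between-arm comparison stated is an unstratified chi-squared test with no interval for the margin. The statistical consequence is minor. Ignoring the strata causes no bias and, taken alone, is at most mildly conservative. The gain in half-width is about 0.005 to 0.09 points under the assumed centre accuracies, and a centre-stratified analysis with the Sato variance showed essentially no gain in power. All of this rests on the planned accuracies, 90 analysed per arm, balance within strata, and assumed centre sizes and effects. The case for the change is consistency with the design and an interval that answers the non-inferiority question, not better precision or protection from centre imbalance.

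**What to change.** Before database lock, state the primary analysis as follows: the difference in diagnostic accuracy, dry minus wet, estimated as a Mantel-Haenszel risk difference stratified by centre only, with a 95% confidence interval suited to sparse strata; non-inferiority is concluded if the lower limit lies above -10 points; the unstratified interval is reported as a sensitivity analysis.

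Name one interval method in advance. The Sato variance and a stratified score interval are both candidates, but they trade off differently. The Sato limit matched the unstratified limit in power, so it may share the excess error seen with Wald limits at the margin. The score interval is the more cautious and may be slightly wider than its unstratified form. A short simulation at the planned counts should settle the choice. Avoid a plug-in stratified Wald standard error, and do not let the observed cell counts decide whether sex enters.

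Cost: a few lines in the SAP, using a variable already recorded. Sex, although a randomisation factor, is left out because the strata would be too sparse. Software other than SPSS 25.0 may be needed; R was already used to generate the allocation list.
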